### Study Aims

The primary aim is to evaluate change in device-measured total and moderate-to-vigorous PA (MVPA), travel mode, and VMT. We expect minutes of MVPA and the proportion of AT (bike, walk, transit) trips, as a share of total trips, will increase. We also expect vehicle trips and VMT will decrease over time in those who live closest to LRT stations, compared to those who have less access to LRT.

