### Covariates and effect modifiers

Sociodemographics include age, sex, race/ethnicity, education, marital status, annual household income, number of adults and children in the household, vehicle access, driving status, caretaking/childcare responsibilities, and years living at address. Health Status will be measured with a subset of the NHANES ‘medical conditions’ survey [104]. An 18-item questionnaire that measures reasons for moving to your neighborhood will be used to adjust for residential self-selection, which is a potential bias in environmental studies [105].

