### Statistical approach

Summary statistics of individual-level demographics, census block attributes, and baseline values of all outcomes will be calculated for the full sample and compared between the LRT exposure groups. Variables that are not balanced across groups will be adjusted for in subsequent analyses. Daily minutes of MVPA are typically positively skewed and will be transformed as needed to better approximate normality. Longitudinal changes in outcomes across the 3 measurement time points will be assessed using multilevel mixed effects linear (for continuous outcomes) or multinomial or ordinal logistic (for categorical outcomes) regression models, with the measurement time point included as an independent variable and adjustment for individual or block group level covariates (i.e., demographic characteristics, walkability, etc.). Covariates will be selected using a priori-knowledge and Directed Acyclic Graphs. Each outcome will be modeled separately. As we will have multiple measurement days nested within participants, a random participant-level intercept will be included in all models (alternative approaches that consider such clustering based on generalized estimation equations (GEE) will be also tested as a sensitivity analysis). We will also test the extent of block group clustering for each outcome (without covariates) by including a random effect for the intercept at the block group level and estimating the intra-class correlation (ICC). A likelihood-ratio test will assess fit between the models with and without clustering and, if significant, a random effect for block group will be included. We will assess effect modification by LRT exposure and other variables on both additive and multiplicative scales (when focusing on binary, categorical or count outcomes) using traditional approaches (stratified analyses coupled with heterogeneity tests or by including an interaction term in our models) [112, 113].

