Due to continued COVID-19 surges, the return to on-campus work has been slower than anticipated. As of summer 2022, student instruction and working arrangements remain an in-person and remote hybrid, making the distribution of devices more challenging. Given COVID-19 safety protocols, limited research staff have been working in-office to answer the recruitment phone line, and many measurement appointments have been rescheduled due to participant illness, childcare duties, or changes in staff scheduling. In response, we’ve expanded our device distribution locations so we can meet participants at more convenient campus locations.

Trolley ridership within the San Diego Region is reported at approximately 80% compared to pre-pandemic periods [124]. Multiple factors beyond the introduction of a new LRT line have likely impacted transit usage during the study period, including increased gas prices and changes in transit pass costs. Our surveys and analyses will attempt to capture and explore these factors.

We anticipate difficulty in achieving recruitment goals across income and racial strata as essential workers and people of color have experienced greater stress and negative health impacts due to the pandemic [125] and may have less capacity to participate. We have identified block groups with high concentrations of poverty and people of color to aid recruitment from these areas during the eligibility screening process. We will additionally employ outreach strategies to staff associations and unions representing diverse campus employees. We’ve met with leaders of these organizations to understand members’ concerns (e.g.., parking costs and availability, work schedules) so we can communicate how the study goals align with their interests. We have also formed an Advisory Board of stakeholders, including UCSD administration and staff/student representatives, staff from the City of San Diego, San Diego Association of Governments (SANDAG), and MTS, and representatives from local climate, mobility, and environmental justice advocacy organizations. We will partner with our extensive, interdisciplinary network of stakeholders to ensure the environmental justice and equity goals of the study are achieved, the research is relevant across sectors, and to share data and findings to help inform future investments in San Diego, California, and nationally.

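### Covariates entered as main effects do not adjust the distance-by-time contrast, so measured confounders of change stay uncontrolled in the main comparison

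*Protocol article*

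**What the plan says.** The Study Aims section of the protocol article expects that "vehicle trips and VMT will decrease over time in those who live closest to LRT stations, compared to those who have less access". For MVPA and active-travel share that section states only an expected increase. The between-group question for those outcomes comes from the Subgroup analyses section, which asks whether change over time depends on distance to light rail. The groups (<1, 1–2 and >2 miles) are defined by home address.

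The Statistical approach section models change over three time points with mixed models "with the measurement time point included as an independent variable and adjustment for individual or block group level covariates", and "a random participant-level intercept will be included in all models". A block-group intercept is added if a likelihood-ratio test supports it. On imbalance, the section says: "Variables that are not balanced across groups will be adjusted for in subsequent analyses". Covariates are chosen by prior knowledge and causal diagrams; the examples given are demographics and walkability. The Covariates and effect modifiers section adds: "An 18-item questionnaire that measures reasons for moving to your neighborhood will be used to adjust for residential self-selection".

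Interactions are mentioned only for effect modification, through "stratified analyses coupled with heterogeneity tests or by including an interaction term in our models". Inverse probability of treatment weighting (IPTW) is described after this as a technique to be considered in sensitivity analysis, with exposure defined as home <1 mile from a stop.

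**The concern.** The hypothesis concerns a difference in change between self-selected groups. What confounds it is any characteristic that differs between distance groups and also goes with a different time trend. Imbalance in level alone does no harm to this contrast.

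Demographics, walkability and reasons for moving are essentially fixed within a participant. As main effects in a random-intercept model they explain differences in level between people. They take nothing out of differences in change. The undertaking to adjust for unbalanced variables would then be met in form but would leave the key contrast where it was, and an estimate reported as adjusted would in substance be the unadjusted one.

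The design offers little protection elsewhere. All device waves follow the line opening, and the Discussion concedes that no earlier device data exist, so pre-opening trends in device outcomes cannot be compared between groups.

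**Working it through.** The plan gives no figure for confounding of change, so there is none to reproduce. The 3.46 min/day in the Sample size section serves below only as a yardstick.

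**1. Algebra.** For participant *i* at wave *t*, with a fixed covariate x entered as a main effect:

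y(i,t) = group + time + group×time + βx(i) + b(i) + e(i,t)

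The within-person change is y(i,3) − y(i,1). Both βx(i) and b(i) cancel. With complete, balanced data the estimated group-by-time coefficient is

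(mean change, near) − (mean change, far),

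which does not involve x. A block-group intercept cancels in the same way. Models stratified by distance group with main-effect covariates have the same weakness, because each stratum's time effect is again the mean within-person change.

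**2. Bias.** If x carries its own trend, γ per unit of x between waves 1 and 3, then

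bias = γ × (mean x near − mean x far).

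It is zero if either factor is zero.

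**3. Illustration (both inputs assumed).** An imbalance of 0.5 SD and γ = 3 min/day per SD give 0.5 × 3 = 1.5 min/day. Against the planning effect, 1.5 / 3.46 = 43%.

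**4. Simulation.** From the article: 465 participants, three distance groups, three waves, 20% attrition, and 4 to 7 valid days per wave (devices worn 7 days, re-wear requested below 4). Assumed: the two inputs in step 3 and a true group-by-time effect of zero. The table shows the mean estimate for <1 versus >2 miles at wave 3, over 30 datasets per row.

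| Data | Unadjusted | Covariate main effect | Covariate × time |
|---|---|---|---|
| Linear, balanced | 1.570 | 1.570 | 0.08 |
| Linear, 20% random loss, 4–7 days | 1.30 | 1.30 | −0.31 |
| Linear, 20% loss depending on x, 4–7 days | 1.22 | 1.30 | −0.07 |
| Binary outcome, logistic GEE (log-odds) | 0.205 | 0.227 | 0.055 |

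The largest shift from main-effect adjustment in any one dataset was about 1e-12 in the first row, 0.20 in the second, 0.45 in the third and 0.044 log-odds in the fourth. In the second and third rows the standard error was about 1.1 to 1.2. Monte Carlo error of the linear means is about 0.91/√30 = 0.17 in the first row and 1.15/√30 = 0.21 in the next two, so −0.31 is compatible with zero. The logistic row is a marginal model; a mixed logistic model was not simulated.

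**5. Weighting.** Over 60 balanced datasets with the same assumptions, IPTW moved the estimate from 1.50 to −0.01 with three groups, and from 1.10 to −0.04 for <1 mile versus the rest.

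**The case against.** The strongest reply is that the article nowhere restricts covariates to main effects. It is a condensed text, and an analysis plan that is not shown may contain covariate-by-time terms. That stands as a limit on certainty: a reader might infer that the plan rules such terms out, and it does not. But the article does describe the adjustment, and it mentions interactions only for effect modification, so main effects are the natural reading.

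Other replies stand in part:

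- **Stratified recruitment.** Enrolment is stratified by light-rail exposure, income and race/ethnicity. If balance is achieved, those variables cannot produce this bias. The Discussion expects difficulty in meeting the income and racial strata, and walkability, reasons for moving and commute length are not stratified.
- **Modifier analyses.** Sociodemographic variables and walkability will be examined as modifiers of change. These are separate questions, and nothing says the terms enter the distance-by-time model jointly.
- **IPTW.** It would act on the measured confounders, and comparing weighted with unweighted estimates could expose the problem. It remains optional, a sensitivity analysis, and limited to <1 mile versus the rest.
- **Exactness.** Strict invariance fails with dropout, unequal days or logistic models. Covariates re-measured and entered as time-varying could move the estimate.

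Two stronger inferences are tempting. From "As of summer 2022, student instruction and working arrangements remain an in-person and remote hybrid" a reader might infer that differential return to campus is a documented confounder. The article says only that arrangements were hybrid. It does not say that return differed by job, income or distance group. A reader might also take 1.5 min/day as the expected error, but it is arithmetic on assumed inputs.

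**Conclusion.** The point holds as a weakness in how adjustment is specified. On the natural reading, main-effect adjustment for fixed covariates leaves the distance-by-time estimate unchanged in balanced linear data and, on average, close to unchanged with dropout or in the logistic check. Measured confounders of change are thus uncontrolled in the main comparison.

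This does not show that the result will be biased, nor by how much. The size is imbalance times differential trend, and the documents supply neither. The illustrative 1.5 min/day shows only that a moderate combination would matter beside 3.46 min/day. The conclusion rests on two assumptions: that covariates enter as main effects, and that they are effectively constant within person. It should be settled before the main models are fitted.

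**What to change.** In every model that estimates distance-group-by-time, include the interaction of time point with each baseline confounder chosen from the causal diagrams. Candidates are income, walkability and home-to-campus distance. The last is not named among the covariates, although that list is open-ended, and it can be derived from the geocoded addresses. Alternatively, make the IPTW analysis co-primary, with weights defined for all three distance groups.

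The cost is about two parameters per continuous or binary covariate with three waves (two per non-reference level for a categorical one) and a small loss of precision. In the balanced simulation one covariate raised the standard error from 0.913 to 0.929, or 0.929/0.913 − 1 = 1.8%. No new data are needed.

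Any analysis that uses on-campus days should be a sensitivity analysis, shown with and without that variable, because it may lie on the causal path.

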### Data collection

Participants will complete a measurement visit after consenting to participation. Participants will be assessed 3 times during the 2 years they are enrolled in the study; once when first enrolled (2022), 1 year after enrollment (2023), and 2 years after enrollment (2024). All data collection will occur after the opening of the UCSD Blue Line Trolley. However, time 1 survey measures ask participants about commute, PA, and spending behaviors both at the time of assessment and, retrospectively, prior to the pandemic and the new LRT. The campus closure in March of 2020 due to COVID-19 provides a noteworthy reference point to aid recall. The UCSD Exercise and Physical Activity Resource Center (EPARC) distributes accelerometer and GPS devices and instructs participants how to wear the monitors. TROLLEY staff call participants during the wear week to ensure compliance. Links to the online surveys are emailed to participants, and participants receive a $50 gift card after completion of all assessments at each time point.

Study data are collected and managed using REDCap electronic data capture tools hosted at UC San Diego [79]. REDCap (Research Electronic Data Capture) is a secure, web-based application designed to support data capture for research studies, providing: 1) an intuitive interface for validated data entry; 2) audit trails for tracking data manipulation and export procedures; 3) automated export procedures for seamless data downloads to common statistical packages; and 4) procedures for importing data from external sources. Participants are assigned a study ID and all records are coded with the study ID rather than personal identifiers. All device data files will be kept on secure servers at the Social Sciences Computing Facility and data will only be accessible to investigators and project staff.

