### Minutes of MVPA

We will use Actigraph GT3X + accelerometers and process the data with Actilife software (ActiGraph, LLC; Pensacola, FL). Participants are asked to wear the device on a belt on their hip during waking hours for 7 days at each measurement point. Participants are asked to re-wear the devices if not worn for at least 10 h per day for 4 days to ensure data are representative of habitual PA [80–82]. We will use the established cut off of 1952 counts per minute (CPM) to determine minutes of MVPA during analysis [83]. To provide perspective on PA disparities reduction, we will assess the % of participants who meet PA guidelines of 150 min of MVPA per week.

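### For device outcomes modelled as daily or trip records, a participant intercept alone omits the wear-week level, so standard errors for change are too small whenever a participant's level shifts between waves

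*Protocol article*

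**What the plan says.** The Statistical approach section of the protocol article covers change across the three time points with mixed-effects models, "with the measurement time point included as an independent variable". It then gives its reason for a random effect: "As we will have multiple measurement days nested within participants, a random participant-level intercept will be included in all models". Days are therefore the observations, and the stated nesting is days within participants.

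One further random effect is named, above the participant. Block-group clustering is tested by likelihood ratio and, "if significant, a random effect for block group will be included". No wave-within-participant term, random slope for time or residual correlation structure is named. Generalised estimating equations (GEE) appear only as a sensitivity analysis, without a stated variance estimator.

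The Minutes of MVPA section asks participants to "wear the device on a belt on their hip during waking hours for 7 days at each measurement point", and adds: "Participants are asked to re-wear the devices if not worn for at least 10 h per day for 4 days". Under Data collection the waves fall at enrolment and one and two years later. Under Study Aims, change in device-measured PA, MVPA, travel mode and vehicle miles travelled (VMT) is the primary aim, with a comparison by closeness to light rail.

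**The concern.** The device data have three levels: days within a wear week, wear weeks within a participant, and participants. The stated model has two. With only a participant intercept, the correlation between any two days of one person is a single constant, whether the days are adjacent or two years apart.

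A person's level can differ between wear weeks for reasons that the fixed effects do not capture: days on campus, illness, season, childcare, a new commute. The Discussion itself expects gradual uptake of light rail and describes hybrid working and changing schedules. That shift is shared by all days of the week, so averaging more days does not reduce it. The two-level model puts it in the day residual and divides it by the number of days.

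The quantities affected are the within-person contrasts: the time effect and the time-by-distance interaction. For daily PA and MVPA these carry the primary aim. Intervals that are too narrow would make chance differences between distance groups look like an effect of light rail access.

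**Working it through.** **Figures in the plan.** There is none to reproduce. The article gives no variance components for daily outcomes. The SD of 4.6 under Sample size is for weekly minutes and does not separate the levels.

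**Inputs**
- From the article: T = 3 waves; m = 7 days per wave (full wear week) or m = 4 (the re-wear threshold).
- Assumed: total variance 1; participant variance 0.35; wave-within-participant variance vw = 0.05, 0.10 or 0.15; day variance vd = 1 − 0.35 − vw = 0.60, 0.55 or 0.50.

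**Step 1, true variance.** The participant effect cancels from a wave 3 minus wave 1 contrast. Per person:

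Var(true) = 2 × (vw + vd/m)

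**Step 2, variance reported by the participant-intercept-only model.** For a balanced design with many participants, the residual variance is a degrees-of-freedom average of the between-wave and between-day mean squares within a person:

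s² = vd + vw × (T − 1)m / (Tm − 1), and Var(model) = 2 × s²/m

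**Step 3, ratio and type I error.** Ratio = √[(vw + vd/m) / (s²/m)]. Actual two-sided type I error = 2 × [1 − Φ(1.96/ratio)].

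**One case in full** (m = 4, vw = 0.05):
- vw + vd/m = 0.05 + 0.60/4 = 0.2000
- s² = 0.60 + 0.05 × 8/11 = 0.6364, so s²/m = 0.1591
- Ratio = √(0.2000/0.1591) = 1.12; 1.96/1.12 = 1.75; type I error 8.0%

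| Days per wave | vw | vw + vd/m | s²/m | True SE / model SE | Type I error |
|---|---|---|---|---|---|
| 4 | 0.05 | 0.2000 | 0.1591 | 1.12 | 8.0% |
| 4 | 0.10 | 0.2375 | 0.1557 | 1.24 | 11.3% |
| 4 | 0.15 | 0.2750 | 0.1523 | 1.34 | 14.5% |
| 7 | 0.05 | 0.1357 | 0.0907 | 1.22 | 10.9% |
| 7 | 0.10 | 0.1786 | 0.0886 | 1.42 | 17% |
| 7 | 0.15 | 0.2214 | 0.0864 | 1.60 | 22.1% |

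More days per week make the understatement worse.

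**What drives the size.** Only vw/vd matters for these contrasts. The 35% share enters because it fixes vd; the ratios above are 0.083, 0.182 and 0.30. At vw/vd = 0.05 the type I error is 6.9% (4 days) or 8.6% (7 days). At vw = 0 the ratio is exactly 1.

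**Simulation check.** Two distance groups with 248 participants in all (465 × 0.8 × 2/3, from planned enrolment, 20% attrition and equal thirds), 7 days, three waves, no true group-by-time effect, 301 to 322 replicates per setting. Type I error for the wave 3 versus wave 1 group-by-time contrast:

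| vw/vd | Participant intercept only | GEE, robust SEs | Wave-level change |
|---|---|---|---|
| 0 | 6.5% | 6.8% | 6.8% |
| 0.1 | 13.2% | 4.1% | 4.1% |
| 0.3 | 22.3% | 5.0% | 4.7% |

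The simulation standard error at a true 5% is about √(0.05 × 0.95/317) = 1.2 percentage points. The participant-intercept column agrees with the closed form (5%, 12.0% and 22.1%), and the other two columns stay near nominal.

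**The case against.** **The article never says that the participant intercept is the only term.** It is a condensed account, and residual structure is often left to a fuller plan. True as far as it goes. But this is not silence on clustering: the section names the unit, the nesting, the random effect and its reach to all models, then a second random effect for block group. Followed as written, that specification omits a level that the design contains.

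**GEE is already planned.** Clustered on participant with robust standard errors it would be valid, as the simulation shows, and would probably expose a discrepancy. But it is a sensitivity analysis with no stated variance estimator. If the two disagreed, the model with the wrong standard errors would still be the primary one.

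**The size is assumed.** This stands. No variance component is in the article, and at the low end of the range the type I error is 8%, not 22%.

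**Stronger readings that the article does not support**
- A reader might infer that intervals for every primary outcome will be too narrow. Odometer-based VMT, weekly guideline attainment and the surveys give one value per wave, and the share of active trips may be analysed that way too. For these no within-week days are miscounted as independent.
- A reader might apply the figures to travel mode. They are for linear models. A trip-level logistic model for mode has the same structural gap, but its size was not calculated.
- A reader might count the block-group pretest as part of the problem. In a balanced linear model a block-group intercept that is constant over waves cancels from within-person change, so keeping or dropping it does not cause this understatement.

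**Conclusion.** The point holds for device outcomes analysed as daily or trip-level records, above all total PA and MVPA minutes per day. For these the stated random effects do not match the three-wave design, and standard errors for change and for change by distance are understated whenever participants' levels shift between waves beyond the fixed effects. Zero shift is implausible for single weeks a year apart, so the direction is firm.

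The size is conditional. It rests on the assumed shares, on balanced data (the same number of valid days in every wave) and on linear models. The tabulated range is an illustration and not an estimate for this cohort.

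**What to change.** For every model with repeated days or trips per wave, specify one of these as primary:
- a participant-by-wave random intercept in addition to the participant intercept;
- an analysis of participant-wave summaries with an unstructured covariance over the three waves;
- participant-clustered robust standard errors.

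The plan should also state which outcomes enter as daily or trip records and which as one value per wave, so that the scope of the rule is clear.

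This is one line in the model specification and needs no change to recruitment or data collection. The cost is wider intervals: in the illustration, 1.12 to 1.60 times as wide as the stated model would report. The variance components can be reported once the data are in, which shows how much the extra level mattered.

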### Subgroup analyses (effect modifiers)

We will examine whether change in outcomes over time is modified by distance to LRT, sociodemographic, and neighborhood environment (i.e., walkability) variables. We hypothesize those living closer to LRT stations, living in more walkable neighborhoods, or accessing more walkable stations, and low-income staff will improve their health and economic outcomes to a greater extent.

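### Block-group clustering is modelled only if a covariate-free likelihood-ratio test is significant; it should be accounted for in every model, although the effect on error rates is modest

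*Protocol article*

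**What the plan says.** All references are to the protocol article. Under Statistical approach, participant-level dependence is handled unconditionally: "a random participant-level intercept will be included in all models". Block-group dependence is handled conditionally. The plan states "We will also test the extent of block group clustering for each outcome (without covariates"), and does so "by including a random effect for the intercept at the block group level and estimating the intra-class correlation (ICC"). Models with and without this effect are compared by a likelihood-ratio test and, "if significant, a random effect for block group will be included". No significance level or reference distribution is given for that test.

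The same section foresees "adjustment for individual or block group level covariates (i.e., demographic characteristics, walkability, etc".). Under Environmental effect modifiers, the Smart Location variables are block-group measures. Under Subgroup analyses, the question is whether change over time is "modified by distance to LRT, sociodemographic, and neighborhood environment (i.e., walkability) variables". The sensitivity analysis by generalized estimating equations is described for repeated measurement days within a participant, not for block groups.

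**The concern.** The rule treats a non-significant test as evidence that there is no clustering. With a few people per block group, such a test has little power against a modest ICC, so the term can be dropped when it is needed. A coefficient for a variable that is constant within a block group, such as walkability, then gets a standard error that treats neighbours as independent. Because the test is run outcome by outcome, error structures will also differ between outcomes partly by chance.

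The test also looks only at a random intercept. Whatever its result, it gives no information on whether block groups differ in their change over time, and that is the dependence that matters for the planned questions about change by neighbourhood. No other stated analysis covers either gap.

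**Working it through.** **Inputs.** From the article: 465 participants; 20% attrition, so 465 × 0.8 = 372; three time points; a block-group intercept kept only on significance. The article gives no number of block groups, no ICC and no cut-off, so these are assumed and shown as ranges. It also gives no figure on block-group clustering that could be reproduced. Outcomes were simulated as continuous.

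**Step 1: size of the error if the term is dropped.** With N people allocated at random to K block groups, the size-weighted mean cluster size is m = 1 + (N − 1)/K. The design effect for a block-level variable is DE = 1 + (m − 1) × ICC. The ratio of model to true standard error is 1/√DE, and the type I error is 2(1 − Φ(1.96/√DE)). For N = 465 and ICC = 0.05:

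| K | m | DE | SE ratio | Type I error if always dropped |
|---|---|---|---|---|
| 60 | 1 + 464/60 = 8.73 | 1.39 | 0.85 | 9.6% |
| 100 | 1 + 464/100 = 5.64 | 1.23 | 0.90 | 7.7% |
| 250 | 1 + 464/250 = 2.86 | 1.09 | 0.96 | 6.1% |

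**Step 2: how often the test finds the clustering.** Simulated with 465 people, ICC 0.05 and cut-off 3.84 (chi-square, 1 df), detection was 41%, 28% and 16% for 60, 100 and 250 block groups.

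A second simulation used uneven block-group sizes, 4,000 runs per cell, and also the boundary-corrected cut-off 2.71. For 465 people and ICC 0.05:

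| Occupied block groups | Detected, 3.84 | Detected, 2.71 | SE ratio if dropped |
|---|---|---|---|
| 47 | 56% | 65% | 0.74 |
| 92 | 37% | 48% | 0.86 |
| 147 | 27% | 37% | 0.95 |
| 238 | 16% | 25% | 0.97 |

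Over all layouts with 465 or 372 people, detection at ICC 0.02 was 4% to 17% (cut-off 3.84). At ICC 0.10 with 465 people it was 92% and 83% for 50 and 100 candidate block groups; with 372 people it was 82% and 70%.

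**Step 3: error of the rule as written.** The rule keeps the term in the runs where clustering is found, so its error lies below the last column of Step 1. Across the simulations, the type I error for a block-level main effect was about 4.5% to 7.1% under the rule, against about 3.7% to 6.3% if the intercept is always kept.

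**Step 4: time-by-neighbourhood terms.** Three waves with a participant intercept, 3,000 runs per cell, block intercept omitted:

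- Block groups differ only in level: SE ratio 0.99 to 1.02, type I error 4.6% to 5.6%. The intercept cancels from within-person change.
- Block groups also differ in slope (illustrative slope variance 0.02 beside an intercept variance of 0.06, on the simulation's scale): SE ratio 0.72 to 0.84, type I error 10% to 15%. A block intercept alone would not repair this.

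**The case against.** The best case for the plan is that a prespecified test is a defined rule and that its overall cost is small. That stands. Power is lowest mainly where block groups hold few people, and there the standard error is hardly wrong: the ratio is about 0.97 with about 2 people per block group. Where clustering is strong and block groups are well filled, the test usually finds it.

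Some stronger readings are tempting and are not supported:

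- A reader might infer that dropping the intercept makes the planned tests of neighbourhood modifiers too liberal. The Subgroup analyses section asks about change over time, and Step 4 shows that the intercept cancels there.
- A reader might take 7.7% or 9.6% as the plan's error rate. Those figures apply if the term is never included, which is not the rule.
- A reader might think that testing without covariates favours dropping the term. Block-level covariates normally absorb between-block variance, so the empty model tends to favour keeping it. What remains true is that the empty model does not describe clustering in the fitted model.
- A reader might fault the plan for ignoring that the null variance lies on the boundary. The article does not say which reference distribution will be used, and may leave this to a fuller plan.
- The Discussion says "We have identified block groups with high concentrations of poverty and people of color to aid recruitment from these areas", from which a reader might infer cluster sampling. The Recruitment section describes an email to more than 17,000 staff as the primary route, so this was an aid to recruitment and not a sampling stage.

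**Conclusion.** The point holds as a modest one. The rule can drop block-group clustering that is present: at an ICC of 0.05 with 60 to 250 block groups and cut-off 3.84, the test finds it in only about 16% to 41% of runs. Standard errors of block-level main effects, such as a walkability coefficient, are then somewhat too small, with a ratio of 0.74 to 0.97 at that ICC across the layouts examined. Type I error under the full rule stays at or below about 7%.

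For time-by-neighbourhood terms the pretested intercept is beside the point. The exposure there is possible variation between block groups in change over time, which the test does not examine. Nothing in the article shows whether such variation exists, so the 10% to 15% error is conditional on it.

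The direction is secure. The size rests on assumed block-group numbers, size spread, ICC and slope variance, and on continuous outcomes; categorical outcomes were not simulated.

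**What to change.** Under Statistical approach, replace the conditional clause with a sentence to this effect: block-group clustering will be accounted for in every model whatever the result of any test, by a block-group random intercept for main effects and by standard errors clustered on block group (or a block-level random slope for time) for time-by-neighbourhood terms; the ICC will be reported descriptively for each outcome.

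The cost is one sentence, with no extra data or participants. Some models will estimate the block-group variance at zero, in which case the results are those of the model without the term. Some intervals will be slightly wider.
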